### Sample size

The sample size of 60 participants (30 per group) was determined using G*Power software (version 3.1.9.2) based on the input parameters of a power of 0.80, an α level of 0.05, and repeated-measures analyses of variance (ANOVAs) with within-between interaction statistical tests.

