## Abstract

**Background:**

Patellofemoral pain syndrome (PFPS) is a common musculoskeletal condition in young and active adults. Exercise therapy is an essential part of rehabilitation in people with PFPS (PwPFPS). Telerehabilitation is an innovative treatment approach that has been used in several musculoskeletal conditions. This study aims to investigate the non-inferiority of telerehabilitation through a smartphone application, the *Vito App*, compared to face-to-face physical therapy on reducing pain and improving physical function, quality of life, and psychological factors.

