### Study design, randomization, and allocation

The present protocol is a non-inferiority, single-blinded, randomized controlled trial with two parallel groups (face-to-face physical therapy and telerehabilitation groups) and a 1:1 allocation ratio. The ethics committee of AJUMS (IR.AJUMS.REC. 1401.282) approved the protocol and it is registered (no: IRCT20201112049361N1.) in the Iranian Registry of Clinical Trials (IRCT). This study protocol follows the SPIRIT (Standard Protocol Items: Recommendations for Interventional Trials) checklist which is available as an additional file (Additional file 1) [36].

Participants will be randomly assigned to either the control group (face-to-face physical therapy) or the experimental group (telerehabilitation) using the stratified permuted block method (Fig. 1). Participants will be randomly assigned to groups based on age, sex, and level of activity as determined by the Tegner Activity Scale to ensure similarity of these variables. A computerized random allocation sequence with different block sizes (4 and 6) will be provided by an independent investigator who is not a member of the research team. An uninvolved party in the assessment will open the sealed envelopes.

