### Statistical methods

The statistical analysis will be performed by SPSS (Statistical Package for Social Science) version 26.0. Data will be reported as follows: mean, standard deviation, 95% confidence intervals, or frequency and percentiles. Descriptive statistics will be obtained on the demographic and clinical characteristics of the participants. Repeated-measures ANOVA (Analysis of Variance) will be used to determine the effects of the group assignments (telerehabilitation vs. face-to-face), the effects of time (baseline, post-intervention, and 1-month follow-up), and the group-by-time interaction for all the outcome measures. *P*-values less than 0.05 will be considered to be statistically significant in all tests. Missing data will be handled using an intention-to-treat (ITT) analysis approach.

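### The 0.80 power behind n=60 is for detecting a group-by-time difference, so it does not apply to the declared non-inferiority question

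*Protocol article*

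**What the plan says.** The abstract gives the aim: "This study aims to investigate the non-inferiority of telerehabilitation through a smartphone application". The section on study design, randomization and allocation repeats it: "The present protocol is a non-inferiority, single-blinded, randomized controlled trial with two parallel groups". The Discussion frames a favourable result as telerehabilitation being not inferior, and would then offer the app as a substitute for clinic-based therapy. Both the Study aims section and the Discussion expect the two arms to improve alike.

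The Sample size section takes a different basis. The 60 participants come from G*Power, "based on the input parameters of a power of 0.80, an α level of 0.05, and repeated-measures analyses of variance (ANOVAs) with within-between interaction" tests. The Statistical methods section plans the same model. It examines group, "the effects of time (baseline, post-intervention, and 1-month follow-up), and the group-by-time interaction for all the outcome measures", and judges every test at p below 0.05. Neither section compares a confidence limit with a margin.

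**The concern.** A non-inferiority trial succeeds when the data exclude a loss larger than a tolerated margin. A within-between interaction test succeeds when the data show that the arms changed differently, in either direction. These are different events with different probabilities, and the sample size was set for the second while the trial's purpose is the first.

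The risk is in how the result will be read. A reader who sees 0.80 beside a non-inferiority design may take it as the chance of showing non-inferiority. If the interaction is then not significant, that reader may conclude that the app has been shown to be as good as supervised therapy. With 30 per group, a non-significant interaction does not by itself exclude a loss that would matter to patients.

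**Working it through.** **Inputs from the Protocol article.** Total N = 60, 1:1 allocation, power 0.80, alpha 0.05 (sidedness not given), k = 2 groups, m = 3 assessments, expected difference none. The effect size f, correlation ρ, margin, SD and dropout are not printed, so they are varied below.

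**Step 1: the plan's own figure.** For G*Power's within-between interaction (sphericity assumed):

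- λ = f²·N·m/(1−ρ), df1 = (k−1)(m−1) = 2, df2 = (N−k)(m−1) = 58 × 2 = 116 at N = 60.
- f = 0.20 with ρ = 0.3 needs N = 58.
- f = 0.25 with ρ = 0 needs N = 54, and 54/0.90 = 60 after a 10% dropout allowance.
- N = 60 gives 80% power for f = 0.234 (ρ = 0), 0.196 (ρ = 0.3) or 0.166 (ρ = 0.5).

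So 60 is a plausible output of the stated method. It can be neither confirmed nor refuted.

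**Step 2: what that 0.80 is the probability of.** Suppose the arms differ by d SD at both post-treatment visits and not at baseline. The interaction effects are then ±d/3, ±d/6 and ±d/6 at the three times. Their mean square is d²(1/9 + 1/36 + 1/36)/3 = d²/18, so f = 0.236d. At ρ = 0.5, f = 0.166 corresponds to d = 0.166/0.236 = 0.70 SD. Under that assumption the 0.80 is the chance of detecting a difference of about 0.70 SD. If the arms improve equally, as the trial expects, then λ = 0 and the rejection probability is 0.05.

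**Step 3: power of 30 per group for non-inferiority (illustrative).** Assumptions: true difference zero, margin M in units of the single-visit SD, t test with 58 df, noncentrality M/SE, SE = √(2v/30). The variance factor v depends on the analysis:

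- One visit, unadjusted: v = 1, SE = 0.258.
- One visit, baseline-adjusted, correlation 0.5: v = 1 − 0.5² = 0.75, SE = 0.224.
- Mean of two post visits, baseline-adjusted, all correlations 0.5: v = (1 + 0.5)/2 − 0.5² = 0.50, SE = 0.183.

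| Analysis | Margin for 80% power, one-sided 0.025 | Same, one-sided 0.05 | Power at 0.5 SD margin, one-sided 0.025 | Same, one-sided 0.05 |
|---|---|---|---|---|
| One visit, unadjusted | 0.74 SD | 0.65 SD | 48% | 61% |
| One visit, adjusted | 0.64 SD | 0.56 SD | 59% | 71% |
| Two visits averaged, adjusted | 0.52 SD | 0.46 SD | 77% | 86% |

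If 26 per group were analysed (an assumed figure, since no dropout rate is given), the one-visit margins at one-sided 0.025 would be 0.79 SD unadjusted and 0.69 SD adjusted. If the VAS SD were 1.5 to 2.5 points (also assumed), the table's margins would run from about 0.46 × 1.5 = 0.7 points to 0.74 × 2.5 = 1.8 points.

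**The case against.** The strongest reply has three parts.

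First, the article does not claim 80% power to show non-inferiority. It names the interaction test openly and gives 0.80 as an input to it. That is correct. The defect is a test that does not match the aim, not a false statement about non-inferiority power.

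Second, a journal article condenses. The effect size and correlation may stand in the full protocol, and Step 1 shows that ordinary choices land at or near 60. A reader might infer that 60 was miscalculated or cannot be derived; the document does not support that. Condensation does not explain the mismatch itself, however. The article says which test produced the 60, and no added effect size or correlation would turn that into a non-inferiority calculation.

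Third, the illustration depends on choices that the article does not make. One-sided 0.025 at a single unadjusted visit is the least favourable row. One-sided 0.05, baseline adjustment or averaging the two post-treatment visits all improve the picture, and 60 may already include a dropout allowance. This also stands, so the result has to be given as a range.

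**Conclusion.** The point holds in this form: the 0.80 is power to detect a group-by-time difference, and it does not carry over to the non-inferiority question that the trial declares. Non-inferiority power is undetermined because no margin is given to evaluate it against.

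A reader might go further and infer that the trial is too small. The document does not show that. Under the assumptions in the table, 30 per group gives 80% power for margins from about 0.46 to 0.74 SD, depending on alpha and analysis. Whether such a margin is acceptable is a clinical judgement that the article does not report. At a 0.5 SD margin and one visit, power is 48% to 71%. With two averaged, adjusted visits it is 77% to 86%.

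The mismatch follows from the article's own words. The sizes rest on a true difference of zero, correlations of 0.5 where adjustment or averaging is used, and complete data.

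**What to change.** Keep 60, and keep the record of how it was chosen. In the Sample size section, state that the 0.80 refers to the interaction test and is not power for non-inferiority. Then:

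- Designate one primary outcome and time point for the non-inferiority conclusion.
- Justify a margin for it on clinical grounds, independently of the sample size. It should not be solved backwards from 30 per group.
- State the power that 30 per group gives at that margin, with the sidedness of alpha, SD, correlation and dropout labelled as assumptions.
- In the analysis and the report, set the confidence interval for the between-group difference against that margin, and do not read a non-significant interaction as non-inferiority.

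The cost is a rewritten paragraph, a matching sentence in the analysis section and probably a less favourable power figure. No extra patients are needed. Recruitment was already under way when the article was written, so the margin should be fixed without sight of outcome data by arm, and the change should be dated.

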## Discussion

Telerehabilitation can have comparable results compared with face-to-face physical therapy to reduce pain and improve physical function and quality of life in patients with various musculoskeletal problems [46]. Telerehabilitation methods can also save time for both patients and physical therapists [28–32]. Since there are limited studies that have investigated the effectiveness of telerehabilitation in PwPFPS, the present study aims to evaluate the effectiveness of telerehabilitation via a smartphone application named *Vito App* in PwPFPS and to compare its efficacy on pain, physical function, quality of life, and psychological features with face-to-face physical therapy.

As long as PwPFPS are active and young adults, a smartphone application available for exercise therapy at home may be helpful for these populations. Using telerehabilitation methods can increase patients’ adherence to the treatment procedure, and they can actively control their condition and the rehabilitation process [15, 17].

The *Vito App* is an innovative tool for exercise therapy and learning beneficial tips about PFPS. The physical therapist can oversee the patient’s progress, and therapist-patient communication will be enhanced. The exercise therapy program in this study will be based on the guidelines of physical therapy in PFPS, and it consists of stretching, strengthening, balance, and functional exercises. Exercise therapy is the most effective treatment for PwPFPS and can lead to pain reduction and physical function improvements [11–14]. This study takes an important step in treating PwPFPS and reducing the risk of developing patellofemoral osteoarthritis later in life.

Based on our hypothesis, participants in the telerehabilitation group and face-to-face physical therapy group will have the same improvements in clinical and psychological outcomes. If our results indicate that telerehabilitation is not inferior to face-to-face physical therapy, it can be an appropriate alternative for PwPFPS, due to its advantages over face-to-face physical therapy, such as the active role of the patients in managing their condition and the fact that there will be no need to refer directly to the physical therapist. PwPFPS living in rural or remote areas or those who do not have enough time to refer to physical therapy clinics can benefit from telerehabilitation methods. PwPFPS can also continue their exercise program as long as they want to use the *Vito App*, and the physical therapists can always have accessibility to their patient’s condition, and they can monitor their progress.

The present study has some limitations, such as the impossibility of blinding the participants and interventional physical therapists due to the nature of the intervention. Another limitation is the slow internet connection in Iran and application bugs that may hinder participants in the telerehabilitation group from using the application. Additionally, using a smartphone application may exclude participants who do not have access to the internet or smartphones.

## Trial status

The trial was registered on 29 October 2022, under the registration IRCT20201112049361N1. Patient recruitment and data collection are currently ongoing and will continue until the required number of participants is achieved. Recruitment was initiated on 1 November 2022 (study protocol version 1, dated July 2022), and is expected to be completed by the end of November 2023. The results of this trial will be submitted to a peer-reviewed journal after the recruitment completion. The research team will have a meeting every 3 months to investigate possible problems during the research (intervention, tests, and follow-ups). In addition, a supervisor (who is not a member of the research team) has been determined by the ethics committee of AJUMS to monitor the correct conduct of the research.

## Data Availability

The datasets used and/or analyzed during the current study will be available upon reasonable. request to the corresponding author after the main publication of them.

## Abbreviations

PFPS: Patellofemoral pain syndrome
PwPFPS: People with PFPS
VAS: Visual analog scale
KOOS: Knee Injury and Osteoarthritis Outcome Score
HADS: Hospital Anxiety and Depression
PCS: Pain Catastrophizing Scale
IRCT: Iranian Registry of Clinical Trials
mHealth: Mobile health
AJUMS: Ahvaz Jundishapur University of Medical Sciences
APTA: American Physical Therapy Association
AKPS: Anterior Knee Pain Scale
SPSS: Statistical Package for Social Science
ANOVA: Analysis of variance
ITT: Intention-to-treat
